**Methods:**

The prospective VACIS study explores the role of VAE in ensuring the absence of pathology at subsequent surgery and reducing the diagnostic underestimation of breast biopsies for microcalcifications. Patients with suspicious breast microcalcifications up to 15 mm, who are candidates for stereotactic biopsy, will be enrolled and randomised into two groups. The control group will complete the biopsy with typical sampling, aiming to collect some microcalcifications from the target, while the experimental group will focus on the complete removal of the biopsy target (confirmed by mammography on the biopsy table), followed by a second sequence of cleaning samples. Radiograms will confirm lesion removal. Pathologic outcomes at surgery will be compared between the groups, and the percentage of underestimation will be assessed. The sample size is calculated to be 70 patients per group, using statistical tests and multivariate logistic models to detect a significant difference in the absence of pathology. Data collected will include patient age, lesion characteristics, and details of the biopsy, pathology and surgery.

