### Study design

All patients with suspicious breast lesions (BI-RADS ≥3) who are candidates for stereotactic VABB and whose lesions present as microcalcifications (the most common form of low and intermediate-grade DCIS) will be prospectively selected. The radiologists involved in the procedure are all dedicated to breast imaging and have at least 5 years of work experience. Patients with a mammographic lesion measuring less than 15 mm in diameter will be enrolled and randomly assigned into two groups on a 1:1 basis. The randomization data will be securely stored on a password-protected computer at the European Institute of Oncology, accessible only to researchers involved in the study.

In the control group, biopsies will focus solely on sampling a few microcalcifications (fewer than 12 samples) and may not necessarily use an 8G needle. In the VAE group, the lesion will be macroscopically removed using an initial sequence of at least eight samples with an 8G needle, followed by a cleaning sequence of at least four samples. This group will undergo an excisional biopsy (VAE) according to United Kingdom guidelines, which define VAE as a collection of at least 4 grams of tissue with an 8G needle. The VAE will be performed during the same biopsy session without recalling the patient later. Both groups will receive post-procedure mammograms and specimen radiograms. The specimen radiogram is used to separate the specimens with microcalcifications from those without, to assist the pathologist, and to verify that the biopsy procedure has indeed sampled the target microcalcifications. We also have the ability to obtain mammographic images while the patient is still on the biopsy table. For the interventional group, if residual microcalcifications are present, the sampling will continue until they are completely removed. For the control group, the goal is not the complete removal of the target but rather the correct diagnostic procedure, so even if residual microcalcifications remain after the biopsy, the procedure will be concluded.

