#### Exclusion criteria

Patients undergoing other types of biopsies (not stereotactic).Patients whose lesions are not in the form of microcalcifications.Patients who refuse to sign the specific informed consent.Patients whose histological biopsy result is not low/intermediate-grade DCIS.Patients with multifocal and/or multicentric lesions.Patients who will not undergo surgery.For the VAE group only: patients in whom haematoma prevents the continuation of the second sequence of biopsies.

The data to be recorded during the biopsy procedure are listed in Table 1.

**Table 1 tab1:** Data recorded during the biopsy procedure.

Characteristics	
**Age (years)**	**Needle (Gouge)**
**Menopausal status**	7G
Pre-	8G
Post-	10G
**Lesion side**	11G
Right	**Samples (n)**
Left	**Lesion excision**
**Lesion site**	Minimal
Upper-outer	Partial
Lower-outer	Complete
Upper-inner	**Clip**
Lower-inner	Yes
Retroareolar	No
Inner-equatorial	**Clip placement**
Outer-equatorial	On-site
Upper-hemitelic	Dislocated
Lower-hemitelic	**Clip dislocation (from the sampling site)**
**Lesion size (mm)**	Distance (mm)
**Lesion type**	Sector (upper, lower, outer, inner)
Microcalcifications	**VAE**
Architectural distortion	Yes
Lump	No
Asymmetry	**Complications**
**VABB type**	Yes (additional notes)
Stereotactic	No
Tomographic	**Histological findings**
Ultrasound	

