### Statistical analysis

The primary endpoint is to compare the percentage of patients with no detectable pathology at surgery between the group undergoing standard treatment (macroscopical removal of the lesion) and the group undergoing VAE (VAE group). Based on the assumption that macroscopical removal without VAE will result in approximately 20% of patients having no pathology at the subsequent surgery, a sample size of 70 patients per arm is calculated to achieve 90% power to detect a 16% difference between the two treatment groups.

This calculation is based on an inequality test for two independent proportions, assuming a 0.2 proportion under the null hypothesis (standard treatment group) and a 0.04 proportion under the alternative hypothesis (VAE group). The test statistic will be the two-sided Z test with pooled variance, using a significance level 0.05.

Continuous variables will be summarized with the median and interquartile range for each treatment arm, while categorical variables will be presented as frequency and percentage. Differences between the two groups will be evaluated using the Wilcoxon rank-sum test for continuous variables and the chi-square test for categorical variables. Multivariate logistic regression models will be used to assess the association between the treatment group and the absence of pathology at surgery, adjusting for key clinical variables and potential confounders. The results will be quantified in terms of odds ratios (Ors), with statistical significance evaluated using *p*-values and a significance threshold set of 0.05.

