Our study aims to identify patients for whom active surveillance can be safely recommended, thereby increasing the enrollment in non-operative management of DCIS. The role of VAE as a potential alternative to surgery has already been successfully investigated for benign lesions and, in preliminary stages, for high-risk lesions (19). We believe that its role in managing *in situ* lesions could be equally promising.

One of the study’s strengths is the integration of VAE on the same day and during the same session as the conventional biopsy procedure. This method offers significant time and economic savings and reduces psychological stress for the patient. However, this protocol will likely result in performing VAE in many patients who do not have *in situ* pathology, as the histological outcome is not known at the time of the biopsy. We believe the risks associated with VAE are minimal and not significantly higher than those of the standard stereotactic procedure. Anyway, the percentage of hematomas and peri-biopsy complications will be recorded and compared between the two groups.

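### A haematoma exclusion that applies to the VAE arm only, after randomisation, probably favours VAE by an amount the protocol does not allow one to fix

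*Protocol article*

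**What the plan says.** The abstract says that patients "who are candidates for stereotactic biopsy, will be enrolled and randomised into two groups", and Study design says that they "will be enrolled and randomly assigned into two groups on a 1:1 basis". The Discussion adds that VAE takes place in the same session as the biopsy and that histology is unknown at that point. Allocation therefore comes before any sampling.

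In the VAE arm, Study design describes an initial sequence that removes the lesion macroscopically, "followed by a cleaning sequence of at least four samples". The control procedure has no second sequence.

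The last exclusion criterion reads "For the VAE group only: patients in whom haematoma prevents the continuation of the second sequence of biopsies". The other exclusions, including those for biopsy histology, multifocality and no surgery, are worded for both arms.

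Under Statistical analysis, "The primary endpoint is to compare the percentage of patients with no detectable pathology at surgery". The article also plans to compare biopsy underestimation between arms. On safety, the Discussion says that "the percentage of hematomas and peri-biopsy complications will be recorded and compared between the two groups", and names no population for that comparison.

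**The concern.** The criterion can only take effect once the assigned VAE has begun, and only in the VAE arm. It removes procedures that could not be completed, while a control patient with a haematoma stays in. What is then estimated in the VAE arm is clearance among completed procedures, set against clearance among all otherwise eligible controls.

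This matters because the trial asks whether VAE could replace surgery for some patients. For that question, a VAE that had to be stopped is one outcome of the strategy. Covariate adjustment in the planned logistic model cannot bring back patients who are not in the data set. Because the rule is written as an eligibility criterion, it may also mean that their surgical pathology is never collected, and a later analysis plan could not repair that. The underestimation comparison would lose the same patients.

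**Working it through.** **Inputs from the article (Statistical analysis).** The control rate comes from "assuming a 0.2 proportion under the null hypothesis (standard treatment group". The VAE rate is given as "a 0.04 proportion under the alternative hypothesis (VAE group". The difference reproduces: 0.20 − 0.04 = 0.16. For an endpoint of no pathology, however, 0.04 would mean that VAE clears fewer patients than control. I therefore use 0.20 + 0.16 = 0.36 as the VAE rate that the hypothesis seems to intend. That is an inference. (By the stated two-sided pooled test, 0.20 against 0.04 needs 85 per arm for 90% power, not the stated 70. That is a separate matter, and the bias formulas below do not use it.)

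**Assumptions, not in the article.**
- h is the share of otherwise eligible VAE patients whose haematoma stops the second sequence: 5%, 10% or 15%.
- q is the proportion of those patients with no pathology at surgery: 0%, 10% or 20%. The upper value is the article's figure for macroscopic removal without VAE.

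**Case A: no true effect.** All VAE patients together have a rate of 0.20, as do controls. After the exclusion the VAE rate reads (0.20 − h·q)/(1 − h).

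| h | q = 0 | q = 10% | q = 20% |
|---|---|---|---|
| 5% | 21.1% | 20.5% | 20.0% |
| 10% | 22.2% | 21.1% | 20.0% |
| 15% | 23.5% | 21.8% | 20.0% |

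The spurious gain is 0 to 3.5 points. For the two-sided pooled Z test, the chance of a significant result in favour of VAE should be 2.5%. At h = 10% and q = 0, with 70 randomised and otherwise eligible per arm (63 left in the VAE arm), D = 0.0222, SE under the null = 0.0708 and SE under the alternative = 0.0709. The chance is then P(Z > (1.96 × 0.0708 − 0.0222)/0.0709) = P(Z > 1.64) = 5.0%. With 150 per arm (135 left) it is 6.7%.

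**Case B: the retained VAE rate is 36%.** With the stopped patients kept, the rate is (1 − h)·0.36 + h·q.

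| h | q = 0 | q = 10% | q = 20% |
|---|---|---|---|
| 5% | 34.2% | 34.7% | 35.2% |
| 10% | 32.4% | 33.4% | 34.4% |
| 15% | 30.6% | 32.1% | 33.6% |

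The shift is 0.8 to 5.4 points, so a 16-point difference becomes 10.6 to 15.2 points. If q equals the retained rate of 36%, the shift is zero.

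**Haematoma comparison, only if the exclusion applies to it.** Suppose a true rate of 10% in both arms, and let a share s of VAE haematomas stop the second sequence. The VAE rate then reads (0.10 − 0.10·s)/(1 − 0.10·s). For s = 25%, 50% and 75% this gives 7.7%, 5.3% and 2.7%, against 10% in controls.

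**The case against.** Five points can be made on the other side.

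- **The lesion is already out.** The stop occurs during the second sequence, after the first has removed the target macroscopically. If such patients clear at the article's 20%, Case A shows no spurious gain and Case B a shift of only 0.8 to 2.4 points. This stands. A reader might infer a certain bias of several points, but that needs q near zero, which the documents do not support. The direction rests on the protocol's premise that cleaning adds clearance. It is plausible but not proven.
- **Other exclusions also act after randomisation.** A reader might infer that every control patient stays and that this criterion alone breaks the randomised comparison. It does not. The histology and no-surgery exclusions remove patients from both arms once the biopsy result or the surgical decision is known. What is particular to this criterion is that it applies to one arm.
- **The haematoma comparison.** A reader might infer that the Discussion contradicts the exclusion. That is possible but not shown, because no population is named. The sentence follows a remark about patients without in situ disease who will still undergo VAE, so it may well cover everyone biopsied.
- **Severity.** Calling the lost events the worst haematomas has no support. The criterion is not graded; it says only that sampling could not go on.
- **A legitimate question.** Clearance after a completed VAE is worth estimating. That supports a secondary analysis, but not making it the only basis of the primary comparison.

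**Conclusion.** The point holds in this form: the article fixes an exclusion that applies to one arm, acts after randomisation and is triggered by the assigned procedure, and nothing in it returns these patients to the VAE arm. The exclusion probably favours VAE. Under the assumed ranges the effect is 0 to 3.5 points if VAE has no benefit, and 0.8 to 5.4 points if the retained rate is 36%. The larger figures are upper ends that require 15% stopped and none of them clear, and the effect is nil if stopped patients clear as often as completed VAEs. Both h and q are assumptions, and 36% is inferred against a printed 0.04. For safety, the conclusion is conditional: if the exclusion also defines the population for complications, haematomas that stopped the procedure are lost from the VAE arm only.

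**What to change.** 1. Remove the VAE-only haematoma exclusion from the primary analysis. Analyse otherwise eligible patients whose second sequence was stopped in the VAE arm, using their surgical pathology, for both the primary endpoint and the underestimation comparison.
2. Keep the exclusion only in a sensitivity analysis labelled per-protocol.
3. State that haematomas and other complications are compared in all randomised patients whose biopsy was started, whatever the histology.

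The cost is one criterion removed and two sentences on analysis populations. Study design already sends patients with low- or intermediate-grade DCIS to surgery, and Table 1 already records complications, whether VAE was done and the extent of excision, so no procedure is added. The VAE estimate may be slightly less favourable. The change removes the arm-specific bias. It does not restore a full as-randomised comparison, because the histology and no-surgery exclusions remain.

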### Statistical analysis

The primary endpoint is to compare the percentage of patients with no detectable pathology at surgery between the group undergoing standard treatment (macroscopical removal of the lesion) and the group undergoing VAE (VAE group). Based on the assumption that macroscopical removal without VAE will result in approximately 20% of patients having no pathology at the subsequent surgery, a sample size of 70 patients per arm is calculated to achieve 90% power to detect a 16% difference between the two treatment groups.

This calculation is based on an inequality test for two independent proportions, assuming a 0.2 proportion under the null hypothesis (standard treatment group) and a 0.04 proportion under the alternative hypothesis (VAE group). The test statistic will be the two-sided Z test with pooled variance, using a significance level 0.05.

Continuous variables will be summarized with the median and interquartile range for each treatment arm, while categorical variables will be presented as frequency and percentage. Differences between the two groups will be evaluated using the Wilcoxon rank-sum test for continuous variables and the chi-square test for categorical variables. Multivariate logistic regression models will be used to assess the association between the treatment group and the absence of pathology at surgery, adjusting for key clinical variables and potential confounders. The results will be quantified in terms of odds ratios (Ors), with statistical significance evaluated using *p*-values and a significance threshold set of 0.05.

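### With the stated inputs (0.20 vs 0.04, two-sided 0.05, pooled Z test), 70 per arm gives about 84% power, not the stated 90%

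*Protocol article*

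**What the plan says.** The Statistical analysis section of the protocol article gives one power calculation for the primary endpoint, the proportion of patients with no pathology at surgery. It states that "a sample size of 70 patients per arm is calculated to achieve 90% power to detect a 16% difference between the two treatment groups". The assumed proportions are 0.20 in the standard group and 0.04 in the VAE group. On the test it says: "The test statistic will be the two-sided Z test with pooled variance, using a significance level 0.05". It mentions no continuity correction and no allowance for losses.

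The abstract (Methods) repeats the number without the power: "The sample size is calculated to be 70 patients per group". The Study design section gives 1:1 allocation. The opening of Methods and analysis, and the Study design section, separately plan 300 patients, 150 per group. That figure is not tied to any power.

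**The concern.** Sample size, both proportions, test, sidedness and significance level are all printed, so the 90% can be recomputed without assumptions. It does not come out. For a two-sided 0.05 test, 70 per arm is too few, while for a one-sided 0.05 test it is almost exactly the number needed. That pattern suggests a one-sided critical value was used for a test described as two-sided.

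This is the only power figure given for the primary comparison. The ethics committee, and anyone reading a null result, would take the risk of missing the assumed difference to be 10% when it is larger.

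**Working it through.** **Inputs.** n = 70 per arm, p1 = 0.20, p2 = 0.04, two-sided pooled-variance Z test, alpha 0.05, target power 90% (Statistical analysis); 1:1 allocation (Study design).

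**Common terms**
- Difference: 0.20 − 0.04 = 0.16; squared, 0.0256.
- Mean proportion: (0.20 + 0.04)/2 = 0.12.
- Pooled term: √(2 × 0.12 × 0.88) = √0.2112 = 0.4596.
- Unpooled term: √(0.20 × 0.80 + 0.04 × 0.96) = √0.1984 = 0.4454.

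**Attempt to reproduce 90% at 70 per arm, as stated**

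Power = Φ[(0.16 × √n − z × 0.4596) / 0.4454], with z = 1.960.

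At n = 70: (1.3387 − 0.9007) / 0.4454 = 0.983, so power = 83.7%. The stated figure is not reproduced.

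**Sample size for 90%, two-sided**

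n = (1.960 × 0.4596 + 1.2816 × 0.4454)² / 0.0256 = (0.9007 + 0.5708)² / 0.0256 = 2.1655 / 0.0256 = 84.6, so 85 per arm.

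**Same test, one-sided 0.05 (z = 1.645)**
- n = (0.7559 + 0.5708)² / 0.0256 = 1.7603 / 0.0256 = 68.8, so 69 per arm.
- Power at 70: (1.3387 − 0.7559) / 0.4454 = 1.308, so 90.5%. This agrees with the stated figure.

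**Does another two-sided method rescue 90%?**

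| Two-sided 0.05 method | Power at 70 per arm | n per arm for 90% |
|---|---|---|
| Pooled Z, normal approximation (as stated) | 83.7% | 85 |
| Pooled Z, exact binomial enumeration | 87.0% | 77 |
| Unpooled Z, normal approximation | 85.2% | 82 |
| Pooled variance under both hypotheses | 83.0% | 87 |
| Arcsine | 87.4% | 77 |
| Continuity-corrected Z, exact enumeration | 80.5% | 91 |
| Fisher exact | 80.6% | not computed |

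No method reaches 90% at 70 per arm. The most favourable gives 87.4%. The smallest sample size for 90% is 77 per arm, 7 more than stated.

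**The case against.** **The formula overstates the gap.** Exact enumeration of the named test gives 87.0%, with 90% first reached at 77 per arm. This stands: the shortfall is about 3 to 6 points depending on method, and both values should be given. It does not bring the power to 90%.

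**The one-sided explanation is inference.** The article never says a one-sided value was used, and that calculation rounds to 69 rather than 70. This also stands. It explains where the figure probably came from, but the discrepancy does not depend on it.

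**The trial plans 300 patients, so power is ample.** With 150 evaluable per arm, power for 0.20 vs 0.04 would be about 99%. But the article ties the 90% to 70 per arm and does not settle whether the 300 are randomised or evaluable patients. The Discussion says histology is not known at biopsy and expects many VAE patients to have no in situ disease. The eligibility criteria keep only low- and intermediate-grade DCIS patients who go to surgery. If 150 per arm are randomised, 85 evaluable requires a yield of 85/150 = 57%, which the article does not give.

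**The assumed direction makes the figure moot.** The endpoint is absence of pathology, so a fall from 0.20 to 0.04 under VAE contradicts the hypothesis. That is a separate defect and the larger one. It means the corrected figures here are provisional, but correcting the direction while keeping a wrong critical value would carry this error into the new calculation.

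**Conclusion.** The stated power is wrong for the stated inputs. At 70 per arm it is 83.7% by the standard formula and 87.0% by exact enumeration, so the type II error is about 16% or 13% instead of 10%. Power of 90% needs 85 per arm by the formula (15 more than stated) or 77 by exact enumeration (7 more). The result uses only the article's own inputs and assumes that all 70 patients per arm are evaluable; losses would lower it further.

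The practical effect depends on how many of the planned 300 patients can be analysed, which the article does not settle. The published power statement needs correcting in either case.

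**What to change.** Keep the two-sided 0.05 test and correct the Statistical analysis section in one of two ways:
- state that 70 evaluable patients per arm give about 84% power (87% by exact enumeration); or
- state that 85 evaluable patients per arm give 90% power by the standard formula, and change the abstract to match.

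In both cases, name the calculation method and say that the number counts evaluable patients: those with low- or intermediate-grade DCIS who had surgery. Before relying on 150 per arm to supply 85, state the expected evaluable yield.

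Rerun the calculation with the two-sided critical value once the VAE proportion is settled. For illustration, if the 16-point difference were meant as 0.20 vs 0.36 (an assumption), 70 per arm would give about 56% power and 90% would need 164 per arm, more than the 150 planned.

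Restating the power costs one sentence and no patients, leaves the abstract as it is, and gives a less favourable figure. Keeping 90% raises the evaluable target by 15 per arm, 30 in total.

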**Discussion:**

Current surgical treatments for low-and sometimes intermediate-grade DCIS offer limited survival benefits and may hurt patients’ quality of life due to surgery-related complications and associated depression. These lesions often grow slowly and might not become clinically significant, suggesting a need to avoid overtreatment. Improved diagnostics procedures, such as VAE, could help distinguish non-invasive from potentially invasive lesions, reduce biopsy underestimation, enable personalised management and optimise treatment strategies. This study hypothesises that VAE could be a viable alternative to surgery, capable of removing pathology during the biopsy procedure.

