All patients with low and intermediate-grade DCIS histological findings will be included in the study and are expected to be evenly distributed between the VAE and control groups. These patients will undergo surgery, and we will compare the percentage of patients with no pathology (including *in situ*) at the surgery between the two groups to determine if VAE can effectively remove small lesions and potentially serve as an alternative to surgery. The surgical specimens will be radiographed to verify the presence of the post-biopsy clip in the surgical sample. We will also compare the rate of biopsy underestimation of invasive carcinoma between the groups. The surgical tissue sections will be documented to ensure consistency between the two groups.

Our goal is to enroll at least 300 patients in this study. We focus on stereotactic VABB because *in situ* neoplasms predominantly present as microcalcifications, and complete macroscopic removal of the lesion can be more easily verified with mammography rather than ultrasound. The study design is summarized in Figure 1.

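### The sample size enters a lower no-pathology rate for VAE than for control, against the trial's hypothesis, and 90% power at 70 per arm fails on either reading of the rates

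*Protocol article*

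**What the plan says.** All the planning figures stand in the Statistical analysis section of the protocol article.

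- Endpoint: "The primary endpoint is to compare the percentage of patients with no detectable pathology at surgery". A higher value is better.
- Control assumption: "macroscopical removal without VAE will result in approximately 20% of patients having no pathology at the subsequent surgery".
- Size and power: "a sample size of 70 patients per arm is calculated to achieve 90% power to detect a 16% difference between the two treatment groups".
- Rates entered: "assuming a 0.2 proportion under the null hypothesis (standard treatment group) and a 0.04 proportion under the alternative hypothesis (VAE group").
- Test: "The test statistic will be the two-sided Z test with pooled variance, using a significance level 0.05".

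The expected direction is given elsewhere. The Discussion paragraph of the Abstract says: "This study hypothesises that VAE could be a viable alternative to surgery, capable of removing pathology during the biopsy procedure". The Study design section says the surgical comparison is made "to determine if VAE can effectively remove small lesions and potentially serve as an alternative to surgery". The Conclusions section likewise looks forward to VAE removing the disease in most cases.

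The Abstract repeats 70 per group. The opening of Methods and analysis and the Study design section plan 300 patients, 150 per arm.

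**The concern.** The 0.2 in the calculation is the figure that the preceding paragraph labels as the control no-pathology rate. The 0.04 paired with it should be on the same scale, and then VAE would clear 4% of patients against 20% in controls. No statement of purpose in the article expects that.

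Two repairs are possible, and they describe different trials. Either the VAE figure is wrong and should lie above 0.20, or both figures are rates of residual pathology and the sentence about 20% carries the wrong label. The control no-pathology rate is 20% under the first repair and 80% under the second, and the text does not say which is meant.

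The choice affects power even though the difference is 16 points in both cases, because the variance of a proportion depends on its level. At stake is whether the power statement for the primary endpoint can be relied on when the result is read.

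**Working it through.** **Inputs from the Statistical analysis section:** two-sided alpha 0.05 (z = 1.960), power 90% (z = 1.2816), pooled-variance Z test, control 0.20, VAE 0.04, difference 0.16, 70 per arm. Allocation is 1:1 (Study design). No dropout rate is stated and none is applied.

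**Formulas,** with p̄ = (p1 + p2)/2, S0 = √[2p̄(1 − p̄)] and S1 = √[p1(1 − p1) + p2(1 − p2)]:

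- n per arm = [(z_alpha × S0 + z_power × S1) / |p1 − p2|]²
- power = Φ[(|p1 − p2| × √n − z_alpha × S0) / S1]

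**Step 1. The plan's own figure, 0.20 vs 0.04.** p̄ = 0.12, S0 = 0.4596, S1 = 0.4454.

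- n = [(1.960 × 0.4596 + 1.2816 × 0.4454)/0.16]² = [(0.9007 + 0.5708)/0.16]² = 84.6, so 85 per arm, not 70. Unpooled variance gives 82 and a continuity correction 97.
- Power at 70 = Φ[(0.16 × √70 − 0.9007)/0.4454] = Φ[(1.3387 − 0.9007)/0.4454] = Φ(0.983) = 83.7%. Exact enumeration of the pooled Z test gives 87.0%.
- With a one-sided 0.05 test (z = 1.645), n = 69 and power at 70 is 90.5%. Of the variants tried, only this one comes close to the stated figure, and the section specifies a two-sided test.

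**Step 2. Reading (a): 0.20 is the control no-pathology rate and VAE adds the stated 16 points.** The VAE rate of 0.20 + 0.16 = 0.36 is an assumption; the article does not give it. p̄ = 0.28, S0 = 0.6350, S1 = 0.6248.

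- Power at 70 = Φ[(1.3387 − 1.960 × 0.6350)/0.6248] = Φ[(1.3387 − 1.2445)/0.6248] = Φ(0.151) = 56.0% (exact 56.9%).
- n for 90% = [(1.2445 + 1.2816 × 0.6248)/0.16]² = [(1.2445 + 0.8007)/0.16]² = 163.4, so 164 per arm.
- Power at 150 = Φ[(0.16 × √150 − 1.2445)/0.6248] = Φ[(1.9596 − 1.2445)/0.6248] = Φ(1.144) = 87.4%.
- At 70 per arm, 90% power against a 20% control rate needs a VAE rate of about 45%, a gain of about 25 points.

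**Step 3. Reading (b): 0.20 and 0.04 are residual-pathology rates, so no pathology is 0.80 vs 0.96.** Taking complements leaves every variance unchanged, so Step 1 applies: 85 per arm for 90%, and 83.7% at 70 (exact 87.0%).

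- Power at 150 = Φ[(1.9596 − 0.9007)/0.4454] = Φ(2.377) = 99.1%.

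**Summary (two-sided 0.05, pooled Z)**

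| Reading | No pathology, control vs VAE | Power at 70 per arm | Power at 150 evaluable per arm | n per arm for 90% |
|---|---|---|---|---|
| (a) | 20% vs 36% (assumed) | 56.0% | 87.4% | 164 |
| (b) | 80% vs 96% | 83.7% | 99.1% | 85 |

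**The case against.** **It is only a labelling slip.** Reading (b) keeps both numbers, the 16-point difference and the hypothesised direction, and makes a single sentence wrong. It also suits the section's description of the comparator as macroscopic removal of the lesion. This is a fair case, and it is why 56% cannot be presented as the trial's power. It does not rescue the stated figure: on this reading 70 per arm still gives 83.7%, and 90% needs 85.

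**A two-sided test covers both directions.** It can reject in either, and the planned logistic model estimates the odds of absence of pathology, so a VAE benefit would be tested properly. That stands: the analysis is not inverted, and the defect is confined to the planning statement. But power is not symmetric about 20%, so a figure worked out for a fall does not carry over to a rise of the same size.

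**The trial plans 300 patients, not 140.** The eligibility criteria require low- or intermediate-grade DCIS on biopsy and planned surgery, so 150 per arm could mean evaluable patients. Power would then be 87% or 99%. Against this, Study design assigns the groups at the biopsy stage, and the Discussion accepts that histology is unknown at that point. The article does not say how many of the 300 will be evaluable, so the point stays open.

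**A stronger inference to avoid.** A reader might conclude that the trial is badly underpowered, with about an even chance of success. The article does not support that. It needs the assumed 0.36, reading (a) rather than (b), and about 70 rather than 150 evaluable patients per arm.

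**Conclusion.** The point holds as an error in the stated planning assumptions. The rates entered contradict the endpoint label and the hypothesis, and this needs no outside figure to establish. The claim of 90% power at 70 per arm is also wrong under the test the section specifies, whichever repair is chosen.

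The size of the shortfall depends on what was meant. At 70 per arm, power is 56% on reading (a) and 83.7% on reading (b). At 150 evaluable per arm it is 87% and 99%. The 56% and 87% rest on the assumed VAE rate of 0.36. The figures at 150 rest on every planned patient being evaluable, which the article does not state. Direction alone does not explain the discrepancy, since 90% is not reached in the written direction either.

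The statement should be corrected before the power is cited in support of any result.

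**What to change.** 1. State the expected rate in each arm on the endpoint as defined, the percentage with no pathology at surgery.
2. Correct whichever is wrong. If 20% is the control no-pathology rate, replace the 0.04 with the expected VAE rate. If 0.20 and 0.04 are residual-pathology rates, change the sentence saying that macroscopic removal "will result in approximately 20% of patients having no pathology at the subsequent surgery" and give the rates as 80% vs 96%.
3. In either case, recalculate and restate the power under the two-sided 0.05 pooled Z test for the number of evaluable patients expected per arm, and say what that number is. Relabelling the rates while leaving 70 per arm and 90% in place would keep a wrong power statement. Bring the 70 per group in the Abstract into line.

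The cost is a rewording and one recalculation. No extra patients are needed if the power is restated. The stated power becomes less favourable if only about 70 per arm are evaluable.
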